## Abstract

**Background:**

With a prevalence of 3 to 8% among women of reproductive age, severe premenstrual symptoms are very common. Symptoms range from emotional and cognitive to physical changes. Severe symptoms (that is, premenstrual syndrome) can have a strong impact on everyday functioning and quality of life. Impairment can be as serious as that of dysthymic disorders. Many affected women receive either no treatment at all or are unsatisfied with their treatment. Although there is some evidence for the reduction of distress through cognitive behavioural therapy, there are only a small number of randomised controlled trials carefully investigating the efficacy of this psychotherapeutic approach. Thus, this study aims to evaluate the efficacy of a cognitive behavioural self-help treatment for women suffering from premenstrual syndrome.

**Methods/design:**

The study is conducted as a randomised controlled trial. The complex diagnostic assessment includes the completion of a symptom diary over two consecutive cycles and a telephone interview. Eligible women are randomly assigned to either a treatment or a wait-list control group. The intervention is based on cognitive behavioural therapy principles and is provided via the internet. It consists of 14 different modules on which participants work over 8 consecutive weeks. In addition to written information, participants receive email feedback from a clinical psychologist on a weekly basis. Participants assigned to the wait-list receive the treatment after the end of the waiting period (8 weeks). The primary outcome measure is the Premenstrual Syndrome Impairment Measure. Secondary outcomes include the Premenstrual Syndrome Coping Measure, the Short-Form Social Support Questionnaire, the Questionnaire for the Assessment of Relationship Quality, and the Perceived Stress Scale. Data is collected during the premenstrual (luteal) phase at pre-treatment, post-treatment, and 6-month follow-up.

**Discussion:**

So far, there is no study investigating internet-based cognitive behavioural therapy for premenstrual syndrome. The programme approaches the problem of high prevalence in combination with severe impairment and insufficient treatment options.

**Trial registration:**

ClinicalTrials.gov:
NCT01961479, 9 October 2013.

## Background

A large proportion of women of reproductive age suffer from premenstrual symptoms. Some of the typical and frequently reported premenstrual complaints are physical discomfort, affect lability, anxiety, depressed mood, fatigability, hopelessness, and irritability
[1]. The symptoms can lead to severe impairment at work, in social activities, or relationships
[2]. The marital relationship is often impaired most intensely in comparison to other social relationships and activities outside the home
[3, 4]. Quality of life is lowered to a degree comparable to that of dysthymic disorders
[3] and suicidal tendency is increased
[1].

According to the impairment caused by the symptoms, premenstrual syndrome (PMS) can be distinguished from a more severe form, the premenstrual dysphoric disorder (PMDD). PMDD is associated with a higher number, severity, duration, and quality of symptoms
[5]. Consequently, PMS and PMDD can be arranged on a continuum. The central feature of both disorders is the cyclic pattern of symptoms: the symptoms arise during the final premenstrual phase and diminish with or a few days after the beginning of menses.

Only PMDD represents a clinical, diagnostic entity. In the *Diagnostic and Statistical Manual of Mental Disorders*, fourth edition text revision (DSM-IV-TR), PMDD was only included in the appendix at a research criterion stage
[6]. Since DSM-5
[7] PMDD has been outlined as a distinct diagnostic category. (Wording of PMDD criteria in this text is simplified and abbreviated. For exact wording, please consult the DSM-5 manual
[7]). To diagnose PMDD, at least five symptoms out of eleven (including at least one out of the first four affective symptoms) have to be confirmed by prospective daily self-ratings of PMS symptoms in the form of a diary over two consecutive menstrual cycles
[7]. These symptoms include: (1) affective lability; (2) irritability or anger or increased interpersonal conflicts; (3) depressed mood; (4) anxiety or tension; (5) decreased interest; (6) difficulty in concentrating; (7) lethargy, fatigability, or lack of energy; (8) change in appetite; (9) hypersomnia or insomnia; (10) a sense of being overwhelmed or out of control; and (11) other physical symptoms (for example, breast tenderness, pain). The symptoms have to exist in the majority of cycles over the preceding 12 months and must cause significant distress or interference. Symptoms are not an exacerbation of the symptoms of another mental disorder; however, other mental disorders may co-occur. With the inclusion of PMDD in the DSM-5, some changes have been implemented
[8]: "distress" in addition to interference, a more precise timing of the onset and the offset of the premenstrual symptoms, possibility of co-occurrence of other mental disorders, possibility of a provisional diagnosis based on clinical history, and distinctiveness from substance use or another medical condition. In particular, the possibility of a provisional diagnosis is an important change as it allows an earlier diagnosis and thus earlier access to healthcare for suffering women
[9]. Also the extension of the interference criteria with the expression of distress is essential as it takes into account that women may maintain their function with a high level of distress without suffering from interference in functioning
[10].

As already mentioned, PMS does not represent a distinct clinical entity and the distinction between PMS and PMDD remains unclear
[11]. The American Congress of Obstetricians and Gynecologists (ACOG)
[5] suggests some diagnostic criteria for PMS that require only one symptom out of a list of ten affective and somatic symptoms
[5]. They seem to focus more on the impairment and distress than on a specified number of symptoms
[3, 10].

The prevalence of PMS and PMDD differs not only due to differences in severity but also due to differences in methodology and diagnostic criteria
[3]. About 75% of women of reproductive age report at least one premenstrual symptom
[1]; 18% of women of reproductive age suffer from PMS
[1]. Prevalence for PMDD based on the DSM-IV-TR ranges from 3 to 8%
[10], with a 12-month prevalence of 5.3%
[1].

About 85% of women with PMS are considerably impaired and seek treatment
[12], but only 20% receive some kind of psychological treatment
[1]. The direct costs for the healthcare system and especially the indirect costs through the loss of work productivity are striking
[3, 13]: having PMS is associated with an annual increase of $59 in direct and up to $4,333 in indirect costs per patient
[13].

Consequently, given the high prevalence and the negative impact on functioning, effective treatment is needed. Common treatments are pharmacotherapy (for example, antidepressants, anxiolytics, cycle-modifying hormonal agents), lifestyle changes (for example, exercise, dietary recommendations, relaxation therapy), complementary therapies such as nutritional supplements (for example, vitamin D, calcium, magnesium) and natural products (for example, St John’s wort extract, vitex agnus castus extract, evening primrose oil), and cognitive behavioural therapy (CBT)
[14–16].

The Royal College of Obstetricians and Gynaecologists (RCOG) suggests a special treatment regimen for the management of severe PMS which is introduced in the following section
[17]. Although complementary therapies have grown in popularity
[18] there is no compelling evidence for their use
[17, 19]. For lifestyle changes, sufficient randomised controlled trials (RCTs) are lacking as well
[16, 17]. Nevertheless, some evidence exists for lifestyle changes (for example, exercise
[20], dietary recommendations
[21], relaxation therapy
[22]) as well as for nutritional supplements (for example, vitamin D and calcium
[23], magnesium
[24]), and natural products (agnus castus extract
[25]). Both complementary therapy (vitamin B6) and lifestyle changes (exercise) are recommended by the RCOG
[17].

Common cycle-modifying hormonal agents that are used in the treatment of PMS/PMDD are the combined oral contraceptive pill, oestrogen, progesterone, and gonadotrophin-releasing hormone (GnRH). Evidence for the administration of progesterone
[26] as well as for the use of second-generation combined oral contraceptives is lacking; in particular, RCTs are rare
[14]. By contrast, the administration of oestrogen via oestradiol patches or implants
[27] as well as the use of GnRH has proven effective
[28]. However, the named hormonal therapies are associated with severe side effects
[14, 29] which sometimes resemble or intensify premenstrual symptoms
[14]. Regardless, the use of a new combined pill including progestin which has not been derived from testosterone (Yasmin®, Bayer Health Care, Leverkusen, Germany) is promising and its application is thus recommended by the RCOG
[17].

Furthermore, selective serotonin re-uptake inhibitors (SSRIs) are recommended as one of the first-line pharmacological management options
[17]. Four meta-analyses support the efficacy of SSRIs
[30–33]. However, side effects of SSRI treatment
[30, 34] lead to high rates of withdrawal from treatment. Further problems are the high placebo reaction in patients suffering from PMS
[35] and the low responder rate of 40%
[32].

Because of the problems of pharmacotherapy, CBT has been suggested as an additional treatment approach
[36, 37] and has even been named a routine treatment option in the guidelines of the RCOG
[17]. Theoretical substantiation for the adoption of CBT for PMS/PMDD comes from the cognitive model for PMS by Blake and colleagues
[38]. The model emphasizes the importance of cognitive appraisal of the premenstrual symptoms and the associated distress. Here, CBT can intervene by questioning the attributions and by teaching coping skills. In addition, CBT has been shown to be effective for disorders sharing common symptoms with PMS/PMDD (for example, affective and somatic symptom disorder)
[39]. Some studies showed promising results for CBT interventions for PMS/PMDD. In a meta-analysis examining CBT for PMS, nine studies were included
[36]. The authors found medium effect sizes for reducing anxiety and depression. Another meta-analysis, containing 22 studies, revealed small to medium effects for CBT and serotonergic antidepressants concerning different outcomes (for example, mood and functional impairment)
[40]. To date, only a small number of well designed RCTs have investigated the efficacy of CBT for PMS
[36, 39]. Methodological limitations are, for instance, a lack of description of the randomization and treatment procedure, substantial loss to follow-up, and potential reporting bias. Besides, they show partially contradicting findings with unsatisfactory
[40] or lacking evidence
[39] contrasting findings of significant improvement
[36]. Thus, one aim of the current study is to develop a well-designed, CBT-oriented self-help programme and to examine its efficacy for distress reduction in PMS patients.

The high percentage of women being dissatisfied with their actual treatment
[41] reveals the importance of new approaches for treating PMS. Our treatment is conducted as an internet-based programme. This decision was reached for the following reasons. First, an internet-based approach enables us to provide treatment for a greater number of women and can therefore reduce waiting time for patients
[42]. Second, stigma associated with seeing a psychologist and conveying sensitive information to a person can be reduced
[42, 43]. This advantage seems to be particularly important because of taboos and stigmata linked with the topics of menstruation and PMS
[44, 45], the women’s fear and experience of not being taken seriously
[38, 41, 46], and their mainly medically oriented perception of PMS
[38]. Positive effects of internet-based CBT (iCBT) in reducing impairment or symptom severity have been found for several functional syndromes or psychosomatic disorders (for example, pain, headache
[47], or tinnitus
[48]) as well as for depression
[49]. Hence, it is highly probable that an iCBT programme can equally well target the somatic symptoms and the affective symptoms that go along with PMS/PMDD.

This study aims to evaluate the efficacy of an iCBT self-help programme for reducing mental and functional impairment in women suffering from severe PMS or from PMDD and improving their coping strategies. First, we hypothesize that the treatment group receiving the iCBT will show a lower impairment than the wait-list control group. Second, we hypothesize that the treatment group improves its coping strategies in comparison to the wait-list control group.

## Method

### Study design and population

This study will be implemented as an RCT including an experimental group and a wait-list control group. The study is approved by the Ethics Committee at the Department of Psychology of the Philipps University Marburg (2013–09) and was registered under clinicaltrials.gov (NCT01961479). Prior to participation in the research, informed consent was obtained.

Eligible women are between 18 and 45 years of age. They are required to have sufficient knowledge of German and access to the internet. Participants have to meet the DSM-5 criteria of PMDD
[7] or the criteria of severe PMS as outlined in the guidelines of the ACOG
[5].

Exclusion criteria for the study are as follows:Diagnosis of a psychosis or a bipolar disorderDiagnosis of an eating disorderDiagnosis of moderate or severe depressionDiagnosis of somatic symptom disorderParticipation in psychotherapy due to premenstrual symptoms (currently or in the past)Acute suicidal tendenciesBirth of a child or lactation during the last 3 monthsPregnancyGynaecological diseases (hysterectomy, oophorectomy, gynaecological cancer, polycystic ovary syndrome, endometriosis, infertility)Begin or change in taking of antidepressants, benzodiazepines/antipsychotics, combined oral contraceptives, or hormones during the last 3 months

### Sample size and power calculations

Effect sizes of the difference between an iCBT programme for PMS and a wait-list control group cannot be estimated precisely because the combination of these two approaches – CBT and internet-based interventions – for treating PMS has not yet been evaluated systematically.

First, there is currently no internet-based self-help programme for PMS. However, iCBT has been found to be effective for disorders sharing common symptoms with PMDD (for example, affective and somatic disorders)
[39]. Large effects for internet-based treatments with psychologist support for depression and anxiety disorders compared to control conditions were found in a meta-analysis
[49]. The effects found for internet-delivered treatments aimed at health problems (pain and headache) were comparable to the effects for face-to-face interventions
[47].

Second, CBT face-to-face programmes for PMS are not well evaluated and suffer from a limited methodological quality as well
[36, 39]. In one meta-analysis examining CBT for PMS
[36] the authors found medium effect sizes. Small to medium effect sizes were found in another meta-analysis comparing CBT and pharmacological interventions
[40].

By considering the different effect sizes found in the cited studies and the insufficient current state of research, we based our sample size calculation on an expected medium effect size (*f* = 0.25, α = 0.05, power 80%). The validity and retest reliability of two applied tests is evaluated in a pilot study and thus is not known yet. Therefore, we assumed a conservative retest reliability. For a 2 × 2 multivariate analysis of variance (MANOVA) the total sample size is set to *N* = 128.

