### Patient recruitment, randomization and procedure of the treatment

Participants are recruited via articles in newspapers, family doctors and gynaecologists, flyers, and different social networks.

Eligible participants undergo four assessments (see Figure 
1). In the first assessment (t0-assessment), participants fill out a retrospective screening of premenstrual symptoms
[50] according to the DSM-5 criteria
[7]. If participants fulfil the basic inclusion criteria and primary DSM-5 criteria (that is, five premenstrual symptoms including at least one affective symptom), a structured clinical interview regarding comorbid disorders is conducted via telephone. Afterwards, principally eligible participants are invited to complete a daily symptom rating during two consecutive menstrual cycles, as requested by the DSM-5 and ACOG criteria. During one of the premenstrual (luteal) phases within these two cycles, the participants fill in the pre-treatment assessment (t1-assessment) including primary (impairment of premenstrual symptoms) and secondary outcome measures (coping with premenstrual symptoms, social support, quality of partnership, level of stress). If the participants fulfil the diagnostic criteria of a severe PMS or PMDD with regard to the daily symptom rating, they are randomly assigned to either the treatment or the wait-list control group. In addition, they are randomized to one of two psychologists who will be the responsible psychologist throughout the study.

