### Statistical analysis

All analyses of the outcomes will be conducted as intention-to-treat analyses. Between-group changes at post-treatment on the impairment and the use of coping strategies will be calculated by using a 2 (pre-treatment/post-treatment) × 2 (experiment group/waiting list) MANOVA. *Post hoc* comparisons will be applied if clarification of the main effects of the MANOVA is needed. Effect sizes between the groups will be calculated with Hedges’ g.

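### N = 128 gives 80% power for one outcome, one degree of freedom and no losses; the protocol does not support that figure for its MANOVA on impairment and coping

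*Protocol article*

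**What the plan says.** The section Sample size and power calculations reports that "we based our sample size calculation on an expected medium effect size", with the inputs given as f = "0.25, α = 0.05, power 80"%. The retest reliability of two of the instruments was still being studied in a pilot, so the authors write: "Therefore, we assumed a conservative retest reliability". No value follows. The section closes: "For a 2 × 2 multivariate analysis of variance (MANOVA) the total sample size is set to" N = 128. It does not say how many dependent variables the MANOVA has, whether f refers to the group effect, the group-by-time interaction or a multivariate effect, or whether 128 women are to be randomised or analysed.

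The section Statistical analysis describes the test: "Between-group changes at post-treatment on the impairment and the use of coping strategies will be calculated" with a MANOVA whose two factors are time (pre, post) and group. It also states: "All analyses of the outcomes will be conducted as intention-to-treat analyses". Whether impairment and coping enter one joint model or one model each is left open. The PMS-B (impairment) is the only primary outcome; the PMS-C (coping) is listed as secondary.

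**The concern.** The protocol commits itself to a power, a test and a total N, so the three should fit together. The N matches a simpler test than the one a reader would take from the analysis section, and it is met only if every woman provides t2 data. The Background criticises earlier CBT trials for losing many participants to follow-up, and the Discussion says that the symptom diary, which is repeated around t2, demands high motivation. Some loss is therefore foreseeable. If the true power is well below 80%, a null result would be over-read as evidence against a medium effect.

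**Working it through.** **Inputs.** From the protocol: f = 0.25 (f² = 0.0625; d = 0.5 for two equal groups), α = 0.05, power 80%, N = 128. Assumed because the protocol gives no figure: 1:1 allocation, the pre-post correlation r, the correlation ρ between the two outcomes, and the t2 loss. All powers come from the noncentral F distribution with noncentrality λ.

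**1. Reproducing 128.** One outcome, two groups: df = (1, N − 2), λ = N·f². At N = 128, λ = 128 × 0.0625 = 8 and power is 80.1%. At N = 126 it is 79.5%. So 128 is the smallest even total that reaches 80%.

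**2. Loss at t2, same 1-df test at f = 0.25.**

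| Assumed loss | Women analysed | Power |
|---|---|---|
| 0% | 128 | 80.1% |
| one woman | 127 | 79.8% |
| 5% | 122 | 78.2% |
| 10% | 115 | 75.7% |
| 20% | 102 | 70.6% |

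**3. Two outcomes tested jointly.** df = (2, N − 3).
- If f = 0.25 is the multivariate effect, λ is still 8 and power at 128 is 70.6%. Reaching 80% needs N = 158. With 20% loss, power is 59.8%.
- If each outcome moves by d = 0.5, λ = N·f²·2/(1 + ρ). At N = 128 with complete data, power is 95% (ρ = 0), 83% (ρ = 0.5), 80.5% (ρ = 0.6) and 78% (ρ = 0.7). With 20% loss it is 79.5% at ρ = 0.3 and 67.3% at ρ = 0.7.

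**4. Pre-post change, one outcome, d = 0.5 in raw SD units.** The change score has variance 2(1 − r) times the raw variance, so λ = N·f²/[2(1 − r)]. At N = 128 power is 66% (r = 0.3), 73% (r = 0.4), 80% (r = 0.5) and 95% (r = 0.7). At r = 0.5 the divisor is 1 and the required N is again 128. With 20% loss power is 56% at r = 0.3 and 90% at r = 0.7.

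**5. ANCOVA on the t1 value, one outcome, d = 0.5.** The residual variance is (1 − r²) times the raw variance, so λ = N·f²/(1 − r²).

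| r | Change score, N = 128 | ANCOVA, N = 128 | ANCOVA, 20% loss (n = 102) |
|---|---|---|---|
| 0.3 | 66% | 84% | 75% |
| 0.5 | 80% | 90% | 82% |

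**The case against.** The strongest reply is that there is no arithmetic error: 128 follows exactly from the stated f, α and power. That stands. Three stronger readings are also tempting, and the protocol does not support them.

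- **That the MANOVA was left out of the calculation.** The two factors named are time and group. Run on one measure at two time points, the group-by-time test has 1 df, and with λ = N·f² it gives 128. A common alternative convention, λ = 2N·f²/(1 − r), gives N = 66 at r = 0 and 34 at r = 0.5. That shows only that this convention was not used.
- **That the retest reliability was left out.** A change-score test with r = 0.5 gives exactly 128, and 0.5 may be what the authors meant by conservative. The value is unreported; it is not shown to be absent.
- **That 80% power is definitely not delivered.** The hypotheses expect improvement in both impairment and coping. With d = 0.5 on both and ρ up to about 0.6, complete data give at least 80%. A high r would also absorb a 20% loss. Counting every PMS-B and PMS-C subscale as a dependent variable, to argue for a larger shortfall, is speculation: the analysis section names only impairment and coping, and total scores are defined for both.

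It can also be said that the loss rates are assumed, that reminders and telephone calls are planned to limit loss, and that an article may leave an attrition allowance to a fuller document. These points soften the loss argument without removing it. The article states a definite N for a definite power, and that N has no slack at the stated f. Analysing by intention to treat does not recover the information from women without t2 data.

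**Conclusion.** The concern holds in a limited form. N = 128 matches a single-outcome, 1-df calculation with complete data. The protocol does not state the inputs that would carry the 80% over to its MANOVA on impairment and coping, so the claim is unsupported for that test rather than proven false. Depending on the unstated inputs, power at N = 128 with complete data ranges from 66% (change score, r = 0.3) through 70.6% (joint test, multivariate f = 0.25) to 95% (change score at r = 0.7, or d = 0.5 on two uncorrelated outcomes). At the stated f, the 1-df test has less than 80% power as soon as any woman is missing at t2. These figures rest on 1:1 allocation and on assumed values of r, ρ and loss.

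**What to change.** Keep N = 128. Make the primary test an ANCOVA of the PMS-B total at t2, adjusted for the t1 value, and test coping separately as a secondary outcome. This fits the existing outcome hierarchy and uses data already being collected. Restate the power paragraph for that test with d = 0.5, two-sided α = 0.05, a stated r (replaced by the pilot's value once known), a stated t2 loss, and whether 128 is the number randomised or analysed. With 128 randomised, power is 84% (r = 0.3) or 90% (r = 0.5) without loss, and 75% or 82% with an assumed 20% loss.

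The cost is a rewritten power paragraph and a change to the primary analysis text, with no added participants. Recruitment was still open at publication, so the change should be made and dated before outcome data are examined. The downsides are that the restated power may look less favourable than 80%, and that the joint MANOVA is no longer the primary analysis.
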